metronomic studies. An modification of this design with bayesian approach and CRM (continuous reassessment model) modelling has been developed and validated by Bhattacharjee et al. (Data sent for publication) It has been validated through data simulation of docetaxel patients where response rate and biomarker was used for decision making. This model takes into account 2 things, disease control (clinical factor) and proportional decline in circulating endothelial cells (biological factor). In the model proposed by Bhattacharjee et al rather than waiting for 3 patients at each dose level, bayesian approach with CRM modelling enables the users to use lesser number of patients and achieve the results early. In this design the efficacy details of each patient are feed into the model and then the model would predict whether the investigators needs to continue at the same dose level or de escalate the doses. The decision rules for the model can be seen in figure 2. This model uses both factors response to MCT and proportional decline in circulating endothelial cells for decision making. Interestingly though response has been used as primary deciding endpoint. In most of the scenarios especially in oral cancers metronomic chemotherapy leads to disease stabilization. In such cases using disease control rate as an criteria for metronomic chemotherapy seems more suitable. Disease control rate is an combination of complete response, partial response and disease stabilization. The variation in CEC measurement is to the tune of 10% or below hence we have used a proportional decline in CEC level of  $> 10\%$  as a deciding factor.

[figure not shown]

Figure 2 : Decision tree.

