#### Processing of sample

The blood would be processed within 24 hours of collection preferably within 4 hours

**Dilution of blood** : If TLC count is more than 20,000 per microliter than dilution would be used.

If not than then the whole blood with dilution would be subjected to further steps

**Blocking serum ( to inhibit nonspecific antibodies)** : Fc receptor blocking agent incubation for 30 min ( The amount and time would vary according to the kit)

**Incubation with monoclonal antibodies tagged with fluorescence** : 4 degree , 30 min in a dark place (The amount and time would vary according to the kit)

1. CD 146 ( endothelial cell marker, marker also seen on T cells)
2. CD 45 ( Antigen present on T cell but not on endothelial cells)
3. CD 34 ( endothelial and stem cell marker)
4. CD 31 ( Endothelial cell marker but absent in stem cell)

5. CD 133 ( progenitor cell marker)
6. Viability stain (7 AAD) ( apoptosis marker)

**Wash and red blood cell lysis** : Add 2 ml of NH4CL freshly prepared. ( 1X NH4CL=1800 microliter D.water + 200 microliter 10 X NH4CL)

**Run in Flow cytometer** : Instrument for Flow cytometry; 4-6 colour Flow cytometer, FACSCalibur ( Becton & Dickinson, USA)

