#### Interpretation of results

1. 1 million events would be recorded
2. Debris and nonviable cell will be excluded by gating in FSC and SSC plot for 7 AAD
3. Gates would be drawn so that CD 146 + and CD 45 (-/dim) would be selected for further analysis
4. This gated population would be further subjected to gating for selection of CD 34 (+), CD 31 (+) cells
5. These cells would than be gated for CD 133
6. The population of CECs and EPC will be identified as per below
  - a. CECs : CD 146 (+), CD 45 (-/dim), CD 34 (+), CD 31 (+) and CD 133 (-)
  - b. Endothelial progenitor cells : CD 146 (+), CD 45 (-/dim), CD 34 (+), CD 31 (+) and CD 133 (+)
  - c. Cut off value for CD31 (+) would be kept at  $4 \times 10^1$  and at  $1 \times 10^1$  for 7AAD (+); CD146(+) and CD133 (+)

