**Absolute number would be calculated by following formula = (Percentage of positive cells on total events ) / (TLC count)**

#### **ELISA**

##### Procedure

Collection of blood sample : 5 ml of blood sample from peripheral vein in EDTA vacutainer

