## 15 Sample size calculation

**Total sample size** : Stage 1 ( 20-30 patients) + Stage 2 ( 76 patients). In stage the continuous reassessment model will be used hence the sample size would be maximum of 30 and minimum around 20. The exact calculations done in both stages are described below in details.

Stage 1 : Flexible-finite sample based approach will be adopted to select the circulating endothelial cells (CEC) interval boundaries and further to use optimum interval design. During the trial, we will continuously update the posterior estimates of decline in CEC and clinical benefit rate and assign patients to the most appropriate dose combination (Figure 1). The Bayesian adaptive screening design will be used to simultaneously select among possible treatment dose combinations. The design is based on formulating the selection procedure as a Bayesian hypothesis testing problem in which the superiority of each treatment combination is equated to a single hypothesis. During the trial conduct, we intend to use the current values of the posterior probabilities of all hypotheses to adaptively allocate patients to treatment combinations. The dose-finding decision will be decided on the twin endpoints the clinical benefit rate at 2 months and proportional decline in CEC at D8 of first cycle. Figure 2 will be used for decision making.

Stage 2: It was assumed that the 3-month progression-free survival (PFS) rate of a standard cancer therapy is 0.50 (H0). An improvement to 0.60 would be considered clinically significant (H1). Assume both the null and alternative PFS distributions follow an exponential distribution. The 1-sided type I error rate of 0.05 and type II error rate of 0.1. Prior assumption includes a fixed enrollment rate of 3 patients per month. We require a stop of 3 months at the end of Stage 1. The library("OptInterim") has been used to calculate the sample size. A 20%extra patient would be taken to account for lost to follow up data. Hence **a total of 76 ( 63 patients +13 patient) sample size is found suitable to carry out the study for stage II with single arm drug therapy.**

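### The CEC count formula divides by the leucocyte count and takes its percentage over a total that, read literally, includes gated-out debris, so shifts in debris or TLC can distort the CEC decline used in Stage 1

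*Protocol*

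**What the plan says.** The flow cytometry steps are in Protocol section 12.2, under Interpretation of results. Step 1: "1 million events would be recorded". Step 2: "Debris and nonviable cell will be excluded by gating in FSC and SSC plot for 7 AAD". Steps 3 to 6 gate CECs and endothelial progenitor cells (EPCs) from what remains. The line after these steps calculates the absolute number from the "Percentage of positive cells on total events" and divides it by TLC; the formula reads "Percentage of positive cells on total events ) / (TLC count". No other total is defined, and the formula does not mention the gate in step 2.

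On handling, section 12.2 (Processing of sample) says: "The blood would be processed within 24 hours of collection preferably within 4 hours".

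On use, section 15 names the two Stage 1 decision endpoints as "the clinical benefit rate at 2 months and proportional decline in CEC at D8 of first cycle". Section 4.7 sets a proportional decline above 10% as the deciding level, on the ground that "The variation in CEC measurement is to the tune of 10% or below". Neither section says whether the decline is in the percentage or in the absolute number.

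**The concern.** One line of the laboratory procedure has two faults.

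- **Denominator.** TLC counts leucocytes per microlitre. It can scale a proportion to a concentration only if that proportion is taken over leucocyte events. If debris, dead cells and other non-leucocyte events stay in the denominator, the result is scaled by one minus their share. This cancels between baseline and Day 8 only if the share is the same at both visits. Nothing in section 12.2 secures that, and the allowed processing time of up to 24 hours gives it room to vary.
- **Operator.** Dividing by TLC does not give a count, and it reverses the effect of any change in TLC between visits.

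At stake is the accuracy of one of the two endpoints used to choose the methotrexate dose carried into Stage 2.

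**Working it through.** The protocol gives no worked CEC value, so there is no figure of its own to reproduce.

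**Inputs**
- Formula, event count and order of gates: section 12.2.
- Deciding level, a decline above 10%: section 4.7.
- Share d of recorded events that are not leucocytes: not given. Assumed, over a range of 0% to 50%.
- Baseline TLC: not given. Assumed 8,000 per microlitre for illustration; the percentage changes depend only on the TLC ratio.

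**1. Effect of the denominator.** Hold the true number of CECs per leucocyte and the TLC constant. The percentage on all recorded events is then proportional to (1 − d), so

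apparent decline = 1 − (1 − d8)/(1 − d0).

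| d0 | d8 | Apparent decline |
|---|---|---|
| 10% | 15% | 1 − 0.85/0.90 = 5.6% |
| 20% | 25% | 1 − 0.75/0.80 = 6.2% |
| 20% | 28% | 1 − 0.72/0.80 = 10.0% |
| 20% | 30% | 1 − 0.70/0.80 = 12.5% |
| 30% | 40% | 1 − 0.60/0.70 = 14.3% |

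The decline reaches 10% when d8 = 1 − 0.9(1 − d0). That means 0% to 10%, 10% to 19%, 20% to 28%, 30% to 37% or 50% to 55%, a rise of 5 to 10 percentage points. The reverse also holds: if d falls from 28% to 20%, a true 10% decline is hidden, since 0.9 × 0.80/0.72 = 1.00. These figures are the same whether TLC divides or multiplies, so correcting the operator alone does not remove them.

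**2. Effect of the operator.** Hold the percentage constant. Division gives a change of T0/T8 − 1; multiplication gives T8/T0 − 1.

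| TLC at baseline | TLC at Day 8 | By division | By multiplication |
|---|---|---|---|
| 8,000 | 6,000 | +33% | −25% |
| 8,000 | 8,900 | −10.1% | +11.3% |
| 8,000 | 10,000 | −20% | +25% |

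On scale: 0.01% at a TLC of 8,000 gives 0.01/8,000 = 0.00000125 by division, which is not a cell count. Multiplication gives 0.0001 × 8,000 = 0.8 cells per microlitre.

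**3. How often the 10% level could be crossed.** Suppose d is normal at both visits with mean m, standard deviation s and within-patient correlation ρ. With no true change, the chance of an apparent decline above 10% is Φ(−z), where z = 0.1(1 − m)/(s√(1.81 − 1.8ρ)). For m of 20% to 30%:

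| s | ρ = 0 | ρ = 0.5 | ρ = 0.8 |
|---|---|---|---|
| 5 points | 12–15% | 5–7% | 0.4–1% |
| 10 points | 28–30% | 20–23% | 9–13% |

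All of m, s and ρ are assumed. The answer runs from under 1% to 30%, so the protocol does not determine it.

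**The case against.** The strongest reply is that the total could mean the events left after step 2. All later gates are taken from those events, and the text does not expressly say that excluded debris is counted. This stands as a reading. It narrows the denominator point to a formula whose literal sense is wrong and whose intended sense is not stated. Even on the kinder reading, the remaining events are not said to be leucocytes, and the division by TLC is still wrong.

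A reader might go further and infer that debris alone will produce false declines in a known share of patients, that these decide the dose, and that a wrong dose goes forward to Stage 2. The documents do not support that, for four reasons.

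- No debris share or between-visit correlation is given. The 28–30% figure needs both a standard deviation of 10 points and zero correlation. A standard deviation of 10 points would by itself give (1 − d) a coefficient of variation of 10/80 = 12.5% to 10/70 = 14.3%, which sits badly with the measurement variation stated in section 4.7.
- CEC decline is one of two endpoints. Section 4.7 describes response as the primary deciding one, and section 15 bases decisions on posterior estimates of both.
- The decision tree is a figure that is not reproduced in the text at hand, so whether the 10% level applies per patient or per dose level cannot be seen.
- Nothing suggests that debris differs by dose level. Random variation would add noise at every level without favouring one.

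It is also fair to say that a viable-leucocyte denominator is not a complete cure, because TLC counts all leucocytes. This stands and is taken up in the fix.

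**Conclusion.** The point holds in limited form. As written, the formula does not yield an absolute count, because it divides by TLC; this needs no assumption. On the literal reading, its denominator also includes events that the numerator excludes, so a rise of 5 to 10 percentage points in the non-leucocyte share, from a starting share between 50% and 0%, is enough to reach a 10% apparent decline with no biological change. Smaller shifts, such as 20% to 25%, are not enough alone.

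The size assumes constant true CECs per leucocyte and constant TLC, and an event share that the protocol does not give. How often the level would be crossed is therefore unknown and depends strongly on the within-patient correlation between visits. The consequence is added error in one of two inputs to the Stage 1 dose decision. It does not show that the decision would be wrong.

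This goes beyond missing detail: a laboratory following the stated formula would report a wrong quantity.

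**What to change.** Replace the formula in section 12.2 with:

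CEC per microlitre = (CEC events / CD45-positive leucocyte events in the same acquisition) × TLC from the same visit.

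Use the same denominator at every visit and for EPCs. State in sections 4.7 and 15 that the proportional decline above 10% is calculated on this quantity. Correct the operator and the denominator together, since either change alone leaves an error.

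State whether the leucocyte denominator is restricted to viable cells. If it is, the protocol should say that it assumes CECs and leucocytes lose viability at similar rates before processing, because TLC includes leucocytes that may have died by the time of acquisition. Sample age can still bias the result if that assumption fails.

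The cost is small: one line in the procedure and one clarifying sentence on the decision rule. CD45 and 7-AAD are already in the panel, and the study calendar (Table 7) already schedules a complete hemogram before study, at Day 8 of cycle 1, on day 1 of cycles and at progression. No new samples or reagents are needed. Samples already run could be recalculated only if their acquisition files were kept, which the protocol does not say.

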##### Processing of sample

Serum extracted from 5 ml of EDTA blood sample would be processed together at the end of clinical study protocol. Hence these serum samples would be stored at -40 degree celsius.

Sample will be processed as per the individual antibody ELISA kit manufacturers guideline on luminex platform.

## Tissue based markers ( IHC or microarray)

### Analysis of markers of hypoxia and angiogenic markers in tumor tissues by IHC

Positive cells per different fields will be counted and graded and the results will be reconfirmed by two pathologists. Hypoxia status will be evaluated by using antibodies against HIF1 $\alpha$  and its downstream targets carbonic anhydrase IX and VEGF. In addition IHC would be done for SPARC, Thymidine phosphorylase and DLL-4 (Table 1). Human kidney tumor or human placenta will be used as positive controls for the immunohistochemical analysis of HIF1 $\alpha$ .

### Detection of HPV

Over-expression of p16INK4a is a surrogate marker for HPV detection hence the samples will be screened by using antibody (CINtec histology p16INK4a kit) as described by Smeets et al . Positive p16INK4a expression is defined as strong and diffuse nuclear and cytoplasmic staining in 70% or more of the tumor cells. In the cases of positive p16 expression, the presence of HPV genomic DNA in oral tumour samples will be detected by Nested PCR using general primer pair MY09/11 and GP5+/GP6+. DNA from human cervical carcinoma *cell lines* SiHa, CaSki (HPV-16 containing cell line), HeLa (HPV-18 containing cell line) will be used as a positive control. House keeping gene beta globin gene will be used as an internal control to test the amplifiability of the template DNA. HPV positive cervical cancer tissues will be used as a positive control when the tissues will be analyzed by *immunohistochemistry* (IHC). All PCR positive samples will be further analyzed for the presence of transcriptionally active HPV by RNA SCOPE assay.

### Cell proliferation markers by IHC

Ki67 is the nuclear protein and a transcription factor associated with cellular proliferation while Cyclin D1 regulates cyclin dependent kinases which are involved in the regulation of different cell proliferation pathways. Hence these markers will be studied

### Apoptosis markers by IHC

Members of Bcl2 family of proteins, whose members have either proapoptotic (Bax) or antiapoptotic (Bcl2) function, act in part by governing mitochondrial cell death through cytochrome C release. Hence ratio of these proteins will be used to measure the apoptotic index and will be calculated as ratio of no. of Bax positive cell / no. of Bcl2 positive cells.

### Inflammation markers by IHC

Cyclooxygenase 2 (COX2) is the key enzyme in prostaglandin biosynthesis, and is responsible for the inflammation.

### Microarray based Gene Expression Analysis

Global gene expression profiling will be carried out on the tissue samples. RNA will be isolated from the tumor tissue samples using the QIAGEN RNeasy Mini kit according to the instructions of the manufacturer. RNA with RIN value more than 7 will be used for analysis. Gene expression arrays from Agilent Technologies (4x44k) will be used for proposed analysis. The comparison will be carried out analyze the differentially expressed genes before starting the therapy and at the end of the therapy. Results of microarray data will be validated by TaqMan quantitative real-time PCR and immunohistochemistry .

### Microarray based global miRNA profiling of serum.

Total RNA will be extracted from 400µl of serum from patients using a mirVana PARIS kit (Ambion) and finally eluted into 100 µl of preheated (95°C) elution solution according to the manufacturer's protocol. The miRNA microarrays manufactured by Agilent Technologies will be used. There are a total of 1205 human and 144 human viral miRNAs on the Agilent Human miRNA Microarray. Total of 100 ng RNA will be labelled and hybridised using the Human microRNA Microarray Kit protocol. Differentially expressed miRNAs will be validated by TaqMan quantitative real-time PCR (TaqMan MicroRNA Assays; Applied Biosystems).

### Need for multiple biopsies

This genomic analysis will help us to understand the mechanism of action, pathways involved in response and resistance. Three biopsies are required. The reason for these biopsies are

1. The baseline biopsy will help us understand about gene expression in platinum insensitive oral cancers, which genes are upregulated and which are down regulated. This information can not help us in understanding mechanism of action. As the drug exposure has not yet happened. It will gives the baseline state of gene expression in platinum insensitive oral cancers.
2. The biopsy on next visit that is 7th day will then be taken and a gene expression analysis will be done. This gene expression analysis will be compared with the baseline gene expression analysis. This would tell us that after exposure to this combination of MCT\_E which genes are upregulated and which are down regulated. This information will then be used to derive pathways which are upregulated or downregulated post exposure to metronomic chemotherapy. So base on these two biopsies we would get the pathways which are activated or deactivated by MCT ie mechanism of action.

- a. The day 7 biopsy is selected as metronomic molecular actions are genetically expressed by day 6.
3. Now that we would know which pathways are helpful in metronomic action. We would do the third biopsy at progression. The comparison of gene expression of third biopsy would be done with the second one. This will tell us which pathways are responsible for resistance

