### 7.3 Tertiary objective (both stages)

To study gene expression changes in the tumor tissue during MCT-E to identify responders and mechanisms of resistance.

1. To analyze HPV, markers of inflammation, cell proliferation, apoptosis and hypoxia to evaluate the association with treatment response.
2. To identify the transcriptomic alterations and to delineate the genes/gene clusters which are differentially regulated in response to the treatment.
3. To carry out global miRNA profiling in tissue and serum samples to identify miRNAs differentially regulated in response to the treatment.

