## 11 Interventions

### 11.1 Prerequisite for administration of metronomic therapy

Patients meeting the inclusion criteria who give written informed consent will be started on metronomic chemotherapy (MCT) with erlotinib, celecoxib and oral methotrexate. Patients on MCT would be monitored for response (RECIST version 1.1) and toxicity (CTCAE version 4.03) at C1D8, D30 and subsequently monthly till progression. Response at 2 months will be considered for stage 1 study decisions on selection of dose level. In patients with intolerable side effects or progression during MCT (either clinical or radiological), the protocol drugs would be stopped and further treatment would be according to the institutional protocols.

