### 12.2 Laboratory interventions

#### Sample collection:

1. **Tumor tissues will be collected at baseline ( +1 month prior to 2 days post MCT start), C1D8 (+/- 2 days) and at progression.** Fresh(~20-30 mg) and formalin fixed tumor tissues will be used. Tumor content will be assayed and tissues having less than 60% of tumor will not be used for microarray analysis. Fresh tumor tissue will be subjected to extraction of DNA and total RNA while fixed tumor tissues will be used for IHC.
2. **20 ml of blood will be collected (5 ml in 3 EDTA tube and 5 ml in plain tube) at baseline collected at baseline ( +7 days prior to 1 days post MCT start) , C1D8(+/- 2 days) and at progression.** 1 EDTA tube each will be used for Flow cytometry, Microarray and ELISA. Fourth tube will be a reserve. 10 ml of blood will be used for separation of plasma (5 ml) and serum (5ml) which will be stored at -80°C, used for analysis of various parameters.
  - a. PK-PD Sample size collection restricted to stage 1
    - i. 5 ml blood will be collected at each time point. Immediately after collection, blood samples will be kept on ice till they are further process to separate plasma by centrifugation at 4°C. Plasma samples will be stored

at -80°C till further analysis of drug levels (Bioanalysis using LC-MS/MS) and levels of CECs and biomarkers.

| DRUG         | TIME POINTS FOR SAMPLING            | No. of Draws | Cycle and Day |
|--------------|-------------------------------------|--------------|---------------|
| Methotrexate | 0, 0.5, 1, 1.5 , 4, 6, 8, 24, 30 hr | 9            | C1D1,         |

3. **At the time of each monthly D30 (+/- 7 days) follow up 10 ml of blood will be collected in EDTA tube for the first 3 months for Flow cytometry and ELISA .**

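### The resistance step compares the progression biopsy with the day-8 biopsy and leaves out baseline, so it cannot tell loss of the acute drug effect from a newly acquired change; the microarray paragraph names a different contrast

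*Protocol*

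**What the plan says.** All references are to the Protocol.

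- Section 7.3 sets the tertiary objective: "To study gene expression changes in the tumor tissue during MCT-E to identify responders and mechanisms of resistance".
- Section 12.2, Sample collection, takes tumour tissue "at baseline ( +1 month prior to 2 days post MCT start), C1D8 (+/- 2 days) and at progression". No window is given for the progression sample.
- Section 12.2, Need for multiple biopsies, item 2, defines mechanism of action from the day-8 sample: "This gene expression analysis will be compared with the baseline gene expression analysis". The time point is justified by the claim that the molecular actions of metronomic treatment are expressed by day 6.
- Item 3 of the same list opens with "Now that we would know which pathways are helpful in metronomic action" and continues "The comparison of gene expression of third biopsy would be done with the second one". It concludes: "This will tell us which pathways are responsible for resistance".
- Section 12.2, Microarray based Gene Expression Analysis, states another contrast: "The comparison will be carried out analyze the differentially expressed genes before starting the therapy and at the end of the therapy". It does not tie that contrast to resistance.
- Section 11.1 says that in patients with "progression during MCT (either clinical or radiological), the protocol drugs would be stopped".

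**The concern.** Item 3 fixes both a comparator and the conclusion to be drawn from it. The comparator is the sample chosen to show the tumour under acute drug exposure. Suppose the tumour at progression has the same expression profile as at baseline. It then differs from day 8 in every pathway that the drugs moved, and item 3 would read all of them as resistance pathways.

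That pattern can arise in at least two ways. The drugs may have lost their effect under continued exposure, which can be a form of resistance. Or the biopsy may have been taken after the drugs were stopped, so that the effect has washed out. Neither is a newly acquired change, and progression versus day 8 cannot distinguish any of the three.

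The microarray paragraph most naturally supplies the missing baseline contrast, since the only sampling times are baseline, day 8 and progression. As the text stands, two analysts could follow the two paragraphs and report different resistance lists from the same arrays. Resistance is a named objective, and this comparison is the reason given for taking the third biopsy.

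**Working it through.** The Protocol gives no power, alpha or effect size for the expression comparisons, so there is no planned figure to reproduce. The check asks what each contrast would flag.

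**Notation and assumptions.** B1, B2 and B3 are a gene's levels at baseline, day 8 and progression. Noise is assumed independent with equal variance σ² at each biopsy; tests are paired and two-sided. None of this comes from the Protocol.

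**Step 1: an effect present at day 8 and fully lost by progression.**
Let B2 − B1 have expected z = δ. With full return to baseline, B3 − B2 has expected z = −δ and B3 − B1 has expected z = 0. The chance that |z| exceeds the critical value c is Φ(δ − c) + Φ(−δ − c).

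| Threshold | c | δ = 2 | δ = 3 | δ = 4 |
|---|---|---|---|---|
| p<0.05 | 1.96 | 52% | 85% | 98% |
| p<0.001 | 3.29 | 10% | 39% | 76% |
| 0.05/44,000 | 4.87 | 0.2% | 3% | 19% |

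These are the rates for progression versus day 8. Progression versus baseline flags such genes at the nominal level, 5% in the first row. The last row assumes Bonferroni over about 44,000 features, the array format named in the microarray paragraph. Section 16.2 states Bonferroni for the relation of biomarkers to disease control; applying it to the arrays is an assumption.

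**Step 2: the same question at trial-sized n.**
Assume a day-8 effect of 0.5 SD (SD = σ) and complete biopsy triplets in n patients. Then δ = 0.5·√n/√2, which is 1.94, 2.81 and 3.08 for n = 30, 63 and 76. The values of n are the stage 1 maximum and the stage 2 figures from section 15; actual triplets may be fewer. Simulated paired t-tests at p<0.05 gave:

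| n | Effect lost: B3 vs B2 | Effect lost: B3 vs B1 | Effect persists: B3 vs B2 | Effect persists: B3 vs B1 |
|---|---|---|---|---|
| 30 | 46% | 5% | 6% | 47% |
| 63 | 79% | 5% | 5% | 78% |
| 76 | 85% | 5% | 6% | 86% |

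Each contrast is blind to something. Progression versus day 8 flags lost effects, and progression versus baseline flags persisting ones. Both are needed.

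**Step 3: regression to the mean.**
Cov(B2 − B1, B3 − B2) = −Var(B2) = −σ², and each difference has variance 2σ², so the correlation is −0.5. For genes with no true change:
- with no filter, progression versus day 8 at p<0.05 keeps its 5% error rate;
- if only genes with p<0.05 at day 8 versus baseline are carried forward, about 18–19% are flagged, nearly all in the reversing direction;
- with selection at p<0.001 and testing at p<0.05 the figure is 42%, and with p<0.001 at both steps it is 4.2%;
- progression versus baseline on the p<0.05-selected genes is inflated too, to about 17–18%, so changing the comparator does not cure selection.

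**The case against.** Several counter-arguments have force.

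- The microarray paragraph already plans a before-versus-end comparison, and the text on repeat biopsies mainly justifies three samples. A reader might infer that baseline is never compared with progression. The Protocol does not support that. What stands is that this contrast is not built into the resistance inference and the two paragraphs are not connected.
- A reader might infer that regression to the mean will fill the resistance list. That needs the progression step to be limited to genes picked at day 8. The opening of item 3, "Now that we would know which pathways are helpful in metronomic action", hints at such a filter but does not state one, and the inflated rates in step 3 also rest on thresholds the Protocol does not give.
- A reader might infer that the resistance list must largely mirror the mechanism list. That follows only if day-8 effects are real and largely gone by progression, which is not known.
- Loss of effect on a target pathway can itself be resistance, and treatment runs until progression, so day 8 is a reasonable on-drug comparator. This stands. It rules out discarding such genes, but it does not make the single contrast able to identify them.
- The off-drug biopsy is a possibility, not a certainty. Section 11.1 stops the drugs at progression, no interval to the biopsy is given, and the Duration of Therapy text allows some patients to continue after radiological progression.
- The objective is tertiary, and detailed contrasts can be left to an analysis plan. But item 3 states the comparator and the conclusion in the Protocol itself, and another paragraph of the same section differs.

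**Conclusion.** The point holds in a limited form. Item 3 reads progression versus day 8 as resistance without using baseline, and it is not reconciled with the microarray paragraph. That contrast alone cannot separate loss of the acute effect from an acquired change. If a day-8 effect is fully lost, the contrast flags it in 52% to 98% of cases at p<0.05 for expected z of 2 to 4, against 5% for progression versus baseline. At p<0.001 the range is 10% to 76%, and it is lower still under a full-array Bonferroni correction.

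These figures rest on equal independent noise and complete return to baseline. They show what can be mislabelled, not what will be. Regression to the mean is a conditional addition that depends on an unstated filter. Dose selection in stage 1 and PFS in stage 2 are unaffected, so this is a worthwhile, inexpensive correction to a tertiary analysis.

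**What to change.** Rewrite the microarray paragraph and item 3 of the biopsy list as one paired analysis of all three biopsies, with three named contrasts: day 8 versus baseline, progression versus day 8, and progression versus baseline. Report separately the genes or pathways that:

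1. differ at progression from both baseline and day 8 (candidate acquired resistance), giving the direction of each difference, because a partly lost effect lies between the two and can also differ from both;
2. only return from day 8 to baseline (loss of drug effect, which may be resistance or washout);
3. persist from day 8 to progression.

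State whether the progression analysis covers all genes. Do not filter it on day-8-selected genes without correcting for the shared day-8 sample. Record the days from last dose to the progression biopsy, so that washout can be examined.

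The cost is wording, one extra data item and a little more analysis of arrays already planned; no further biopsy is needed. The list labelled acquired resistance will be shorter.
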